**Methods and Design:**

Fifty-seven schools (86% of 66 eligible secondary schools) in Perth, Australia were recruited to the clustered (by school) randomised trial, with even randomisation to the intervention and control arms. Between 2003 and 2006, the VIP program was administered to 1,267 participants in the intervention schools, while 1,567 participants in the non-intervention schools received standard curriculum. Participants were all female and aged between 13-15 years upon recruitment. Pre and post-intervention questionnaires measured short-term impact and participants are now being followed through their teenage years via data linkage to hospital medical records, abortion clinics and education records. Participants who have a live birth are interviewed by face-to-face interview. Kaplan-Meier survival analysis and proportional hazards regression will test for differences in pregnancy, birth and abortion rates during the teenage years between the study arms.

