#### Individual level (student)

Individual participants were females aged 13-15 years of age (in Year 9 or 10) at the time of recruitment. All eligible students in the schools allocated to the intervention group were invited to participate in the VIP program. Students from both the intervention and control groups were invited to participate in a prospective study of teenage pre-conceptual health knowledge and behaviour. The participant flow is described in Figure 1.

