#### 3. Video documentary

The third component of the VIP Program is the "Talking Realities Video". The video was developed specifically for the VIP Program in conjunction with Murdoch University and the Balga Teen Family Centre (a Child Care Centre based within Balga Senior High School to help facilitate teen mothers complete their High School). The video is a documentary series of four non-judgmental interviews with teen mothers talking about their own experiences. Each mother talks about how they got pregnant, their family, friends and general public's reaction to their pregnancy and the practicalities and pragmatics of being a teen mother (i.e. not being able "party like their other friends", family support, financial and educational difficulties, and both the joys and difficulties of parenthood). The Video runs for 30 minutes but is broken into 3 sections so that the School Health Nurse could run 10 minutes of the Video in each of the small group educational sessions (to be run in sessions 2, 3 and 4).

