#### Secondary Outcomes (Participant knowledge, attitude and behavioural change)

Participants were assessed by a self-complete questionnaire to determine whether the program had immediate, short or longer-term impact on participant knowledge and attitudes towards pregnancy and parenting or on their health behaviours. Instruments and measures for the questionnaires were developed from a series of focus groups for the initial pilot project in conjunction with feedback from the health professionals facilitating the pilot project. Questionnaires were administered at enrolment (pre-test), at four weeks post intervention, and again at six months post intervention to glean longer term recall and risk behaviour change.

During the final debriefing (session 4), VIP Program participants (intervention arm) completed a questionnaire assessing the immediate impact of the Program. This included process measures about adherence to the Program and completion of the workbook instructional activities, change in perceptions and attitudes regarding parenting and satisfaction with the Program, and the initial response to the virtual parenting experience and health behaviours during the Program.

The pre-test and four-week post-test and six-month post-test questionnaires were completed by participants in the intervention and control arms of the study. The questionnaires included the following domains: participant demographics, life goals (e.g. importance of finishing high school, or going to university), current health behaviours (physical activity, alcohol consumption, smoking status, fruit and vegetable consumption) as well as readiness to change these behaviours; psychological distress as measured by the Kessler 10 [41]; knowledge about pregnancy and parenting; attitudes to contraception, teenage pregnancy and parenthood; sexual behaviour and contraception use. Additionally, at six months the participants were assessed on measures of impulsivity, venturesomeness and empathy using the Eysenck scales [42].

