### Planned analyses for the Primary Outcome

#### Primary outcome - pregnancy

For live births, the birth date of the baby will be used as the outcome date. For abortions, the recorded admission date for abortion will be used. For overall pregnancies we will estimate the due date of a pregnancy for abortion cases by adding 6 months to the abortion date, as the majority of induced abortions take place in the first trimester. Where more than one pregnancy outcome is detected, the date of the first event will be used. Kaplan-Meier survival analyses will be undertaken for these primary outcomes. To adjust for clustering by school and potential confounding variables, the data will be analysed using Cox proportional hazards regression, using the Lin and Wei robust sandwich estimate of the variance-covariance matrix. All analyses will be undertaken using SAS or SPSS.

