Recruitment bias becomes a threat to the external validity if there are systematic differences in the characteristics of participants in the intervention and control arms that are associated with the exposure or outcome variables. Unfortunately, the study was unable to collect information from the students who did not participate or the parents who failed to provide consent. Therefore we can only anticipate differences between participants and non-participants based on the best available evidence. In general epidemiological studies, participants are more likely to be of higher socioeconomic status, employed, married and of better health status. Further, in studies of risk behaviours, those engaged in those behaviours are less likely to participate [49] The requirement for active parental consent has been associated with the lesser representation of ethnic minorities, students having problems at school and students already engaged in or at risk of problem behaviours [52,54]. So while the study cannot control for systematic differences between participants and non-participants, it can statistically control for potential baseline differences between the intervention and control groups. The following data has been collected by the Trial to investigate and control for potential confounders: socio-economic status, family type, whether the participant had ever had sexual intercourse, had ever had responsibility for caring for a baby, reported importance and intention of going to University or further education, level of psychological distress, and smoking, drug and alcohol use. These variables were measured at the time of entry into the Trial. Additionally each participant's educational attainment data has been linked to the Trial data to enable controlling for academic success.

In conclusion although the pragmatic nature of the trial and the low participation rates will provide some complexities for the analyses, the results will have international significance and advance the evidence to inform school based teen pregnancy prevention programs.

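### Linked educational attainment is named as an adjustment variable but not limited to results from before enrolment, so the adjusted hazard ratio may condition on a consequence of pregnancy

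*Protocol article*

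**What the plan says.** The section on planned analyses for the primary outcome describes the primary model: "To adjust for clustering by school and potential confounding variables, the data will be analysed using Cox proportional hazards regression", with a robust sandwich variance. It names no covariates.

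The Discussion supplies them. It offers adjustment as the response to selective participation, saying of the study that "it can statistically control for potential baseline differences between the intervention and control groups". It lists socio-economic status, family type, sexual experience, experience of caring for a baby, importance and intention of further education, psychological distress, and smoking, drug and alcohol use, and adds: "These variables were measured at the time of entry into the Trial". Only after that sentence does it continue: "Additionally each participant's educational attainment data has been linked to the Trial data to enable controlling for academic success".

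On the source of the education data, the Methods and Design paragraph of the Abstract says that "participants are now being followed through their teenage years via data linkage to hospital medical records, abortion clinics and education records". On age, the Recruitment section says: "Individual participants were females aged 13-15 years of age (in Year 9 or 10) at the time of recruitment". Outcome linkage runs until all participants reach 20.

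**The concern.** A covariate used to control baseline differences has to be fixed before the intervention can act. Attainment stands outside the list that the article says was measured at entry, its source is described as part of follow-up, and the girls were in Year 9 or 10 when recruited, so much of their schooling lay ahead. The natural reading is a covariate recorded at least partly after allocation.

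Such a variable can be changed by a pregnancy, which is the outcome, and possibly by the program. Conditioning on it mixes control of confounding with conditioning on a consequence of the outcome or on a mediator.

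The adjusted estimate matters in this trial. Students knew their arm when they consented, and participation was 58% against 45%. The Discussion calls the resulting potential bias the main limitation and answers it with covariate adjustment. The Sample Size Calculation section would read no difference as failure of the program, so a shift of the hazard ratio towards 1 is not harmless.

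**Working it through.** **Step 1: timing.** Three statements have to be read together.
- Discussion: the listed confounders were measured at entry. Attainment comes after this sentence and is not covered by it.
- Abstract: education records belong to follow-up through the teenage years.
- Nowhere does the article give a date, school year or restriction to results from before enrolment.

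Timing after allocation is therefore inferred, not stated.

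**Step 2: can attainment change after allocation?** The article gives indirect support for two paths.
- Pregnancy to schooling: the video section describes teenage mothers speaking of "family support, financial and educational difficulties, and both the joys and difficulties of parenthood", and mentions a centre that helps them complete high school.
- Program to schooling: the questionnaires used to assess program impact cover "life goals (e.g. importance of finishing high school, or going to university". These are attitudes, so this path is weaker.

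**Step 3: size.** The article gives no figure for this bias, so there is none to reproduce. A simulation shows how the mechanism behaves.

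Inputs from the article: 1,267 + 1,567 = 2,834 participants; expected control pregnancy risk 6% + 10.8% = 16.8%; target reduction 25%, represented here by a hazard ratio (HR) of 0.75.

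Assumed inputs: 5 years of follow-up; a latent academic and social factor U that lowers the log hazard by 0.5 per SD; a direct program effect of *a* SD on attainment; a loss of *b* SD of attainment after a pregnancy. Clustering was left out because it does not drive this bias.

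Model, with A = arm, D = pregnancy during follow-up, and U and e independent standard normal:
- hazard = (0.17/5) × exp(log(HR) × A − 0.5 × U)
- attainment before allocation: L0 = 0.7 × U + 0.714 × e (SD about 1, since 0.49 + 0.51 = 1.00)
- attainment after allocation: L = L0 + a × A − b × D

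For each of 200 replicates per setting, Cox models were fitted with A and L0, and with A and L. The simulated control risk was 16.9% to 17.2%. The Monte Carlo standard error of the log hazard ratio adjusted for L was 0.006 to 0.008.

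| a | b | True 1.00: adjusted for L0 | True 1.00: adjusted for L | True 0.75: adjusted for L0 | True 0.75: adjusted for L |
|---|---|---|---|---|---|
| 0 | 0 | 1.002 | 1.002 | 0.752 | 0.752 |
| 0 | 0.5 | 0.995 | 0.994 | 0.748 | 0.752 |
| 0 | 1 | 1.003 | 1.006 | 0.755 | 0.785 |
| 0.2 | 0 | 1.000 | 1.071 | 0.747 | 0.801 |
| 0.1 | 0.5 | 0.996 | 1.076 | 0.754 | 0.822 |
| 0.2 | 0.5 | 1.003 | 1.166 | 0.762 | 0.892 |
| 0.2 | 1 | 1.003 | 1.230 | 0.752 | 0.962 |

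**Step 4: reading the table.**
- Attainment fixed before allocation: essentially no bias in any row.
- Pregnancy path only (a = 0): nothing under the null; a true 0.75 becomes 0.752 with b = 0.5 and 0.785 with b = 1.
- Direct program effect on attainment (a > 0): 1.07 to 1.23 for a true 1.00, and 0.80 to 0.96 for a true 0.75.

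**The case against.** The strongest reply is that the article never says the attainment results postdate allocation. That the records have been linked tells us when they were joined, not when the results were obtained. The word that sets attainment apart may only separate linked data from questionnaire data, and the stated purpose, control of baseline differences, fits results from before enrolment. The remark also sits in the Discussion and speaks of enabling control, while the analysis section names no covariates. An article may leave the final covariate list to a fuller document.

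Much of this stands. A reader might infer that the plan commits to adjusting for a variable measured after randomisation; the text supports this only as its natural reading. If only earlier results are meant, the bias concern falls away. The point is still more than missing detail, because the article names the covariate, states its use and describes its source as follow-up data.

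The second reply concerns size. The large shifts need a direct effect of a six-day program on attainment. No program objective or study hypothesis concerns attainment, and no figure in the article supports such an effect. That stands. A reader might also infer that the result could move in either direction, but every appreciable shift in the table is upward, which works against a false claim of benefit. A program that lowered attainment was not simulated.

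The third reply is that academic ability may truly differ between arms, given unequal participation and the Discussion's own remark that active parental consent under-represents students with problems at school. The simulation contains no such imbalance, so it does not weigh the confounding that attainment would remove. This stands too, and it argues against simply dropping attainment.

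**Conclusion.** The point holds in a limited form. As described, linked attainment is an intended adjustment variable that nothing restricts to results from before enrolment. If later results enter the Cox model, the model conditions on something that pregnancy, and possibly the program, can change, and the adjusted hazard ratio can be biased.

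The size is unknown. With a pregnancy effect alone, the shift is nil under the null and small to modest otherwise, at most 0.75 to about 0.79 in the cases run. Anything larger rests on an assumed direct improvement of attainment by the program. The documents do not support a claim that the primary result will be materially distorted, or that attainment must be excluded altogether.

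Severity: should be fixed. Confidence: moderate, because the timing is inferred.

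**What to change.** State in the covariate definition that the primary Cox model uses only attainment results dated before enrolment, or before the student knew the school's allocation. Where a participant has no such result, rely on the covariates measured at entry, which already include importance and intention of further education. Keep later attainment for an outcome analysis or a labelled sensitivity analysis.

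The cost is one sentence and a date filter on records already linked. The downside is that some participants may lack an earlier result, with some loss of control for academic ability; their number should be reported by arm.

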## Abbreviations

VIP: Virtual Infant Parenting; IS: Infant Simulator; WA: Western Australia; TICHR: Telethon Institute for Child Health Research; ICC: Intra-class correlation; BTIO: Baby Think it Over; CONSORT: Consolidated Standards of Reporting Trials; WADLS: Western Australian Data Linkage System; HMDS: Hospital Morbidity Data System; SHN: School Health Nurse; GP: General Practitioner/Doctor
